## 4. Expected Results

Recruitment began during the third quarter of 2024 and is expected to run for 6 to 9 months, with final data collection anticipated within the first quarter of 2025. Data analysis and interpretation should be completed by the final quarter of 2025.

Upon completion of this study, the expected results will (1) identify neural response patterns derived from temporally decomposed components (eMMN, lMMN) that differentiate ASD and TD groups, particularly highlighting reduced variance explanation and weakened factor scores in the ASD group; (2) clarify differences in single-feature discrimination and multi-feature integration between the two groups, with specific emphasis on diminished sensitivity to increasing feature complexity in ASD, with the most pronounced group differences observed in dual- and triple-feature condition; (3) evaluate the fit of theoretical models of speech integration using Representational Similarity Analysis (RSA); and (4) reveal temporal dynamics of neural integration by examining how the similarity between neural RDMs and theoretical models evolves across the MMN time window. We expect that neural representational structures in the TD group will align more closely with an “Integrated Features” model, while the ASD group may show a stronger fit with a “Segmental-Only” model, supporting a local processing bias. We also expect that group differences in representational structure will become more pronounced in the late MMN (lMMN) period, reflecting delayed or disrupted higher-order integration in ASD. These results will provide a comprehensive, multi-level understanding of how children with ASD process and integrate speech features in a tonal language context.

## 5. Discussion

This research protocol is designed to investigate how Mandarin-speaking children with ASD process and integrate multiple phonological features (consonants, vowels and lexical tones), across varying levels of complexity. As the data are not yet fully analyzed, the purpose of this discussion is not to present conclusions, but to contextualize the study’s design, its potential contributions, and the interpretive frameworks that will be used to evaluate the findings once data collection and analysis are complete.

The central innovation of this research lies in its tiered, multi-feature oddball paradigm, which allows for the systematic comparison of neural responses to single-, dual-, and triple-feature speech deviations within a single, efficient experimental session. This approach moves beyond the traditional focus on isolated acoustic contrasts and instead probes the dynamic integration of segmental and suprasegmental cues—a process fundamental to natural speech perception, especially in tonal languages like Mandarin, where pitch variations directly determine lexical meaning.

The pattern of results will be evaluated against two complementary sets of predictions. If the theory-driven framework (EPF/WCC/NCH) is supported, we expect to see a dissociation: relatively intact or enhanced neural responses (e.g., MMN amplitude, factor scores) to single-feature deviants (e.g., consonant-only, vowel-only), but attenuated or delayed responses to multi-feature deviants (e.g., V + T, C + V + T). This pattern would align with models that posit a cognitive style in ASD characterized by heightened local sensitivity paired with impaired global integration. It would suggest that children with ASD can detect individual phonetic cues but struggle to bind them into unified, linguistically meaningful percepts. If the data-driven framework (MMN literature) is supported, we expect to see a graded, complexity-dependent deficit: reduced MMN amplitudes and prolonged latencies across all conditions, with the most severe effects in multi-feature and tone-involving contrasts. This would be consistent with the Neural Complexity Hypothesis and would suggest a more general processing burden in ASD, where increasing feature complexity leads to cumulative degradation in neural responsiveness, regardless of a local/global distinction. If the results reveal a mixed or unexpected pattern (e.g., no group difference in tone processing), this would highlight the heterogeneity within the ASD population and challenge the universality of current models. Such findings would prompt a re-evaluation of assumptions about what constitutes “local” or “global” processing and could point to subgroup-specific profiles (e.g., based on language ability or sensory preference) that are not captured by broad theoretical frameworks.

A key aspect of our analysis is the inclusion of hemispheric asymmetry as a data-driven prediction. While EPF, WCC, and NCH do not explicitly predict reduced left-hemispheric specialization, the MMN literature suggests that children with ASD may show less lateralized or right-shifted MMN responses to speech sounds. If this is confirmed, it would provide critical evidence for atypical neural organization in ASD, one that may underlie broader difficulties in processing rapid, temporally precise linguistic cues.

We employ two analytical approaches, temporal PCA and RSA. t-PCA decomposes the ERP waveform into latent components (e.g., early and late MMN), isolating overlapping neural responses and increasing sensitivity to group differences, particularly valuable in pediatric data where peak latency and morphology can vary. By extracting factor scores, we can compare the strength and timing of neural responses across conditions and groups. For instance, if two ERP components (such as an early and late MMN) overlap in the 200–300 ms range, t-PCA can help disentangle them into separate factors, allowing us to assess each one’s magnitude in ASD vs. TD children.

In contrast, RSA examines the multivariate structure of neural representations. It quantifies the dissimilarity between brain responses to different stimuli, creating a representational dissimilarity matrix (RDM). We compare empirical RDMs to theoretical models (e.g., “Integrated Features” vs. “Segmental-Only”) to test whether children with ASD represent speech features differently. This approach moves beyond univariate amplitude/latency measures to assess how features are bound into coherent percepts. For example, one model RDM might predict that changing the lexical tone produces large neural dissimilarity (if tone is a salient feature) whereas changing the consonant with the same tone produces a smaller dissimilarity. Another model might predict that any two-feature change (tone + vowel together) yields a bigger neural distance than single-feature changes. We will correlate these model RDMs with the empirical RDMs derived from the EEG data for each group. If TD children’s neural patterns correspond closely to the model emphasizing multi-feature integration, but ASD children’s patterns do not, this would directly support the idea that the ASD group encodes speech features differently. In essence, RSA will tell us how information is represented in the neural activity of each group—whether the brain treats combined feature changes as the sum of their parts or as a unique, salient event, and how this differs between ASD and TD. This multivariate approach is valuable because it moves beyond examining individual ERP peaks and considers the holistic neural response to speech stimuli as a pattern that can be compared to cognitive models.

While the multi-feature oddball paradigm is well-validated in developmental and clinical populations, we acknowledge that detecting fine-grained differences in MMN is challenging. Our analytical approach is designed to maximize sensitivity, but the results must be interpreted within the context of known variability in ASD and the inherent limitations of EEG. Foundational studies [62,81] demonstrated that multi-feature paradigms efficiently detect various speech-sound differences with comparable or superior sensitivity to traditional paradigms, using shorter recording times. More recent work [1,2] has refined these paradigms to capture fine-grained phonetic and prosodic contrasts, sensitive to individual variability in language and musical experience. Critically, studies applying this approach in children at risk for dyslexia [63], children with Asperger syndrome [82], and very young children or infants [83,84], confirm the method’s reliability across ages and populations. Cross-linguistic applications [85] and recent work on emotional prosody [65,86] further demonstrate its feasibility in capturing subtle speech-feature processing differences across linguistic and developmental contexts. Building on this empirical foundation, we employ advanced analytic approaches (t-PCA, RSA) to further enhance sensitivity by isolating latent neural components and distributed representational patterns, thereby increasing the likelihood of detecting group-level differences even when univariate effects are small.

Our carefully matched ASD and TD sample allows us to examine how factors like language ability, symptom severity, and developmental stage modulate neural processing. Testing these predictions in Mandarin, a tonal language where pitch is lexically meaningful, enables a critical test of whether atypical auditory processing in ASD stems from integration deficits (WCC) or enhanced feature detection (EPF)—a distinction with direct implications for intervention. While both EPF and WCC predict reduced responses to multi-feature deviants, they diverge on single-feature processing: EPF predicts enhanced or intact responses, while WCC does not. However, we acknowledge that the existing MMN data suggest that the notions of local vs. global and segmental vs. suprasegmental processing may be oversimplistic. The outcomes may reflect additive or interactive influences among different phonological features.

Regardless of the specific outcomes, this study will provide valuable insights into the neural mechanisms underlying speech perception differences in ASD. If integration deficits are confirmed, it could inform the development of culturally and linguistically tailored interventions that explicitly train children to bind acoustic cues. If local processing advantages are found, interventions could leverage these strengths to support language learning. Furthermore, by focusing on a tonal language, this research addresses a significant gap in the literature, which has largely been based on non-tonal languages. Findings may reveal whether the unique demands of tonal processing amplify or mitigate the typical auditory processing profile in ASD.

In summary, this study protocol combines a sensitive EEG paradigm with advanced analyses to investigate whether atypical speech processing in ASD arises from disrupted feature integration. Our protocol and proposed analyses are intended to contribute much-needed data that can help clarify which aspects of speech sound processing pose the greatest challenges for children with autism. Findings may inform culturally tailored interventions and lay the groundwork for using neural signatures as biomarkers for early language risk.

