### 3.2. Data-Driven Predictions (Based on MMN Literature)

Predictions are also derived for the t-PCA and RSA analyses from empirical findings across multiple studies (Table 2). They reflect general patterns in the literature and serve as a baseline against which theoretical predictions can be evaluated. They do not assume a local/global dissociation but rather a graded, complexity-dependent deficit.

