#### 3.2.1. t-PCA-Level Predictions

P7 (Amplitude Attenuation): Across all conditions (with the exception of vowel deviation), the ASD group will show lower factor scores for MMN components, with the most severe reductions in multi-feature conditions.

P8 (Latency Prolongation): Peak latencies of eMMN and lMMN components will be systematically delayed in the ASD group, with delays increasing as feature complexity rises.

P9 (Component Blurring): The temporal separation between eMMN and lMMN components will be less distinct in the ASD group, suggesting a breakdown in the normal cascade of auditory processing stages.

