**Figure 3 brainsci-15-00905-f003:**
[figure not shown]
Workflow of RSA applied to ERP data from a multi-feature oddball paradigm.

**Table 1 brainsci-15-00905-t001:** Tentative Predictions for the Seven Stimulus Conditions (Based on EPF/WCC/NCH) Condition.

	Processing Type	Prediction in ASD	EPF + NCH Account	WCC + NCH Account
Consonant only	Local	↑ or = MMN amplitude ↓ or = MMN latency	Enhanced perception of phonetic detail	Intact
Vowel only	Local	↑ or = MMN amplitude ↓ or = MMN latency	Enhanced formant processing	Intact
Tone only	Global	↓ MMN amplitude ↑ MMN latency	Reduced prosodic integration	Impaired due to global integration load
C + V	Mixed/Global	↓ MMN amplitude ↑ MMN latency	Disruption due to multiple feature load	Integration weakness
V + T	Global	↓↓ MMN amplitude ↑↑ MMN latency	Disrupted holistic processing	Poor feature binding
C + T	Global	↓↓ MMN amplitude ↑↑ MMN latency	Disrupted holistic processing	Failure to form unified percept
C + V + T	Global	↓↓↓ MMN amplitude ↑↑↑ MMN latency	Collapsed integration under complexity	Strongest integration failure

Note: ↑ represents significant increase. ↓ represents significant decrease. = represents similar results when comparing MMN responses in ASD group with those in the TD group. Double/Triple arrows indicate magnitude increment/decrement.

**Table 2 brainsci-15-00905-t002:** Specific Predictions Based on MMN Literature-Based Predictions for Each Stimulus Condition.

Condition	MMN Amplitude in ASD	Latency in ASD	Reduced Left-Hemispheric MMN Dominance
Consonant only	↓	↑	Predicted—based on broader speech processing literature
Vowel only	= or ↓	↑	Predicted—but may be less pronounced than for consonants
Tone only	↓	= or ↑	Predicted—particularly for lexical tones
C + V	↓↓	↑↑	Predicted—likely pronounced
V + T	↓↓	↑↑	Predicted—key for tonal languages
C + T	↓↓	↑↑	Predicted—reflects integration challenge
C + V + T	↓↓↓	↑↑↑	Predicted—most pronounced reduction expected

Note: ↑ represents significant increase. ↓ represents significant decrease. = represents similar results when comparing MMN responses in ASD group with those in the TD group. Double/Triple arrows indicate magnitude increment/decrement.

**Table 3 brainsci-15-00905-t003:** Phonological Stimuli: Standard vs. Deviant Feature Variations.

Stimulus Type	Stimulus	Feature(s) Changed
Standard	/ba1/	None
Deviant 1	/ba4/	Tone change
Deviant 2	/bu1/	Vowel change
Deviant 3	/da1/	Consonant change
Deviant 4	/bu4/	Tone + Vowel Change

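### The Discussion lists tone among the worst effects under the data-driven account, but at equal feature count the plan's own tables make a tone excess a theory-driven prediction

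*Protocol article*

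**What the plan says.** Section 5 sets the interpretive rule: "The pattern of results will be evaluated against two complementary sets of predictions". For the theory-driven account (EPF/WCC/NCH) it expects intact or enhanced single-feature responses, "but attenuated or delayed responses to multi-feature deviants (e.g., V + T, C + V + T"). For the data-driven account it expects reduced MMN amplitudes and "prolonged latencies across all conditions, with the most severe effects in multi-feature and tone-involving contrasts".

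The condition-level predictions stand elsewhere:

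- **Table 1, theory-driven** ("Tentative Predictions for the Seven Stimulus Conditions (Based on EPF/WCC/NCH) Condition"): consonant only and vowel only are enhanced or equal. Tone only has one arrow of deficit. C + V has one arrow ("Mixed/Global ↓ MMN amplitude ↑ MMN latency"). V + T and C + T have two, and C + V + T has three.
- **P2, theory-driven** (section 3.1.1): factor scores are reduced particularly where tone changes.
- **Table 2, data-driven** ("Specific Predictions Based on MMN Literature-Based Predictions for Each Stimulus Condition"): C + V, V + T and C + T all read ↓↓ and ↑↑. Tone only reads ↓ for amplitude, like consonant only, and '= or ↑' for latency.
- **P7, data-driven** (section 3.2.1): lower factor scores except for vowel, "with the most severe reductions in multi-feature conditions". P8 has delays that grow with feature complexity. Neither singles out tone.
- **Section 3.2**, on the data-driven set: "They do not assume a local/global dissociation but rather a graded, complexity-dependent deficit".

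**The concern.** The study is built to weigh two accounts against each other, and research question 4 in section 1.4 asks specifically whether tone-related conditions show the largest differences. If such a tone excess appears, the reader must know which account it supports. The tables and P2 say theory-driven. The interpretive paragraph names tone under the data-driven account and not under the other. A deficit that is larger in V + T and C + T than in C + V could therefore be reported as support for the account whose table predicts equality there. The same paragraph also says the data-driven pattern would hold regardless of a local/global distinction, although section 1.4 classes tone as global.

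**Working it through.** The plan gives no figure to reproduce here. The check codes the arrows as ordinal deficit ranks: one, two or three arrows of deficit = 1, 2, 3; '=' = 0; enhanced = −1; 'or' entries kept as ranges.

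| Condition | Table 1 (amplitude and latency) | Table 2 amplitude | Table 2 latency |
|---|---|---|---|
| Consonant only | −1 to 0 | 1 | 1 |
| Vowel only | −1 to 0 | 0 to 1 | 1 |
| Tone only | 1 | 1 | 0 to 1 |
| C + V | 1 | 2 | 2 |
| V + T | 2 | 2 | 2 |
| C + T | 2 | 2 | 2 |
| C + V + T | 3 | 3 | 3 |

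**Tone excess with two features changed:** mean(V + T, C + T) minus the C + V cell.
- Table 1: (2 + 2)/2 − 1 = **+1**, for amplitude and for latency.
- Table 2: (2 + 2)/2 − 2 = **0**, for amplitude and for latency.

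**Tone excess with one feature changed:** tone only minus the mean of consonant only and vowel only.
- Table 1: 1 − 0 = +1, up to 1 − (−1) = +2.
- Table 2 amplitude: 1 − 1 = 0, up to 1 − 0.5 = +0.5. Any excess comes from the vowel exception.
- Table 2 latency: 0 − 1 = −1, up to 1 − 1 = 0.

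**Without matching on feature count:** Table 2 amplitude averages (1 + 2 + 2 + 3)/4 = 2.0 in the tone cells and (1 + 1 + 2)/3 = 1.33 in the others, or 1.0 if vowel is '='. But the tone cells change 2.0 features on average and the others 1.33, so this gap reflects feature count.

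**Three readings of the Discussion phrase against Table 2:**
1. Every multi-feature contrast and every tone contrast is in the severe class. C + V then equals V + T and C + T, as in Table 2. But tone only joins the severe class, whereas Table 2 gives it the same amplitude arrow as consonant only and the mildest latency entry.
2. Only contrasts that are both multi-feature and tone-involving are severe. V + T and C + T then exceed C + V, against Table 2.
3. Tone adds to feature count. Both conflicts arise.

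**Power of the two-feature contrast.** Assumptions not in the plan: within-child correlation r = 0.5 between conditions, a true group difference of 0.3–0.5 SD, two-sided α = 0.05. The plan's 30 per group gives 58 df.
- Sum of squared weights: 0.5² + 0.5² + 1² = 1.5.
- SD of the contrast: √((1 − 0.5) × 1.5) = 0.866.
- Noncentrality at 0.3 SD: (0.3/0.866) × √15 = 1.34, power 26%.
- Noncentrality at 0.5 SD: (0.5/0.866) × √15 = 2.24, power 59%.
- 95% interval half-width: 2.00 × 0.866 × √(2/30) = 0.45 SD.

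**The case against.** The strongest reply is that the sentence is loose prose in an exploratory paper. It carries no arrows and never compares V + T or C + T with C + V. On average Table 2 does have more arrows in the tone cells, and its only triple-arrow cell involves tone. There is no scoring rule, the theory framework is called provisional, and section 6 offers the findings as preliminary. The data-driven set also does stress tone, in P12 and in the hemispheric column of Table 2.

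Part of this stands. The phrase is ambiguous, and nothing is mechanically scored. But section 5 names tone-involving contrasts in addition to multi-feature ones. If it meant only the average gap that feature count produces, the words would add nothing, and each reading that gives them content conflicts with some row of Table 2. The tone emphasis in P12 and the last column of Table 2 concerns left-hemisphere asymmetry, which section 5 takes up in a separate paragraph; the sentence at issue concerns amplitude and latency.

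A reader might infer more: that under the Discussion wording both accounts predict the same group-by-condition interaction and differ only in level. The documents do not support that. It requires one particular coding of the prose (feature count plus tone), and it requires consonant and vowel in Table 1 to be read as '=' when the entry also allows enhancement. Nor is the two-feature contrast the only separator. Consonant only is enhanced or equal in Table 1 and reduced in Table 2, and vowel only separates the accounts in part.

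**Conclusion.** The interpretive rule for the data-driven account is wrong as written, in a limited way. For MMN amplitude and latency, a tone excess at equal feature count is a theory-driven prediction (Table 1, P2). Table 2 does not predict it, apart from the possible half-arrow in single-feature amplitude that the vowel exception allows. The size is one arrow against none in the two-feature cells. This rests only on the order of the arrows, which the plan leaves without a value in µV or ms.

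The consequence is possible misattribution of one result pattern, not loss of the ability to tell the accounts apart. A null result in the two-feature contrast should not be read as support for Table 2: no effect size is attached to an arrow, and under the assumptions above the interval would reach about 0.45 SD either side of the estimate.

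**What to change.** 1. In section 5, remove the tone-involving wording from the data-driven amplitude and latency pattern so that it agrees with Table 2, P7 and P8. Keep the tone emphasis for hemispheric asymmetry (P12).
2. In the same section, state the tone excess under the theory-driven pattern, in line with Table 1 and P2.
3. Before the analysis is completed, state that the ASD–TD difference will be estimated with confidence intervals for (a) mean(V + T, C + T) minus the C + V cell, (b) tone only minus the mean of consonant only and vowel only, and (c) consonant only. Say that a larger ASD deficit in (a) favours Table 1.
4. Do not count a null result in (a) for Table 2 unless an effect size is fixed in advance. State that power for (a) is modest, with the assumptions behind the figure.

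The cost is a few sentences and one pre-stated set of contrasts, with no new data. Since section 5 says the data are not yet fully analysed, the report should also say when the contrasts were fixed.

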##### Step 3: Comparing Neural RDM with Theoretical Models

To assess how well neural responses align with theoretical models, we compute Spearman’s rank correlation between each neural RDM and the candidate theoretical RDMs. This comparison is performed separately for each time window (eMMN, lMMN, P3a). For group-level comparisons, we conduct the RSA separately for individuals with ASD and TD groups to examine potential differences in how speech features are neurally represented. We use permutation testing combined with cluster-based correction to control multiple comparisons and assess significant differences between groups.

These models assume that phonological features contribute additively to auditory dissimilarity, consistent with the view that early auditory encoding tracks separable acoustic dimensions (e.g., pitch, formant structure, place of articulation) without strong nonlinear interactions. The use of weighted models reflects the hypothesis that tone, vowel, or consonant cues may be differentially salient in perception—especially in tonal languages like Mandarin. While interactive or nonlinear RDMs could in principle be constructed (e.g., hierarchical cue interactions or phonological feature geometry), they require stronger theoretical constraints and larger datasets to validate. Thus, the current additive scheme balances theoretical interpretability, perceptual relevance, and statistical robustness. We employed RSA because it extends beyond univariate amplitude analyses by leveraging multivariate patterns of neural responses, allowing detection of distributed representational differences even when traditional ERP measures yield weak or non-significant effects. This approach is highly suitable for multi-feature paradigms, as it can capture subtle shifts in neural encoding across complex feature combinations and evaluate their alignment with theoretically derived perceptual models [80].

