#### 3.1.2. RSA-Level Predictions

P4 (Representational Structure): Neural representational dissimilarity matrices (RDMs) in the ASD group will show weaker differentiation between multi-feature deviants (e.g., C + V + T vs. standard) compared to TD children, particularly in the lMMN time window.

P5 (Integration Failure): The fit between neural RDMs and a theoretical “Integrated Features” model (which assumes synergistic processing of C, V, T) will be poorer in the ASD group, especially for V + T and C + V + T conditions.

P6 (Local Bias): The fit between neural RDMs and a “Segmental-Only” model (prioritizing C and V) will be stronger in the ASD group than in TD children, reflecting a local processing bias.

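### The Discussion reads RSA fit in TD without fit in ASD as direct support for different encoding, without tying this to the planned between-group test, and that test on raw Spearman fits is itself sensitive to group differences in noise

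*Protocol article*

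**What the plan says.** Section 2.3.4, Step 3, takes Spearman's correlation between each neural RDM and each theoretical RDM, in three windows (eMMN, lMMN, P3a). It then says: "we conduct the RSA separately for individuals with ASD and TD groups to examine potential differences in how speech features are neurally represented". The next sentence names a between-group test: "We use permutation testing combined with cluster-based correction to control multiple comparisons and assess significant differences between groups".

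The RSA predictions are worded as group contrasts. P5 (section 3.1.2) expects that fit to the integrated model "will be poorer in the ASD group, especially for V + T and C + V + T conditions"; P6 and P11 expect a stronger fit to other models in ASD than in TD. Section 4 expects that "neural representational structures in the TD group will align more closely with an “Integrated Features” model".

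Section 5 then says how a result would be read. It takes the case where the TD group fits the integration model well, and says that if the ASD group's "patterns do not, this would directly support the idea that the ASD group encodes speech features differently". The sentence gives no threshold for close correspondence and does not mention the Step 3 test. The opening of section 5 presents the Discussion as the interpretive frame in which the findings will be evaluated.

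**The concern.** A within-group fit test has the null hypothesis that this group's RDM is unrelated to the model. The research question has another null: that fit is the same in both groups. Passing the first test in TD and failing it in ASD says nothing direct about the second. Two identical groups will often split this way by chance, and more often if one group's recordings are noisier.

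There is a related weakness in the direct comparison. Raw Spearman fit falls as measurement noise rises, even when the underlying representation is unchanged. Permuting group labels tests whether the fits are exchangeable, so noisier ASD data can yield a significant group difference with no difference in structure. Unequal noise is plausible: the ±75 µV rejection rule in section 2.3.1 can leave unequal trial counts, and section 6 warns that ERP variability may affect the consistency of RDM construction.

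At stake are P5, P6 and P11 and expected results (3) and (4) in section 4. A chance split or extra noise would look like the predicted integration failure.

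**Working it through.** **Inputs from the protocol.** 30 children per group (section 2.1.2); 8 stimuli (section 2.2.1), hence 8 × 7 / 2 = 28 pairs; Spearman fit and three windows (section 2.3.4, Step 3); α = 0.05, stated only for the sample-size calculation (section 2.1.1). The protocol gives no power or error rate for the RSA, so there is no figure of its own to reproduce.

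**Assumptions.** Within-group power p; noise levels; identical additive encoding in both groups; 10 measurement dimensions in the noise simulations; t-tests standing in for label permutation.

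**Step 1: TD-only pattern, equal power.** With independent groups and identical encoding, P(TD significant, ASD not) = p(1-p).

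| p | p(1-p) |
|---|---|
| 0.2 | 16% |
| 0.5 | 25% (maximum) |
| 0.7 | 21% |
| 0.8 | 16% |
| 0.9 | 9% |
| 0.95 | 4.75% |

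Simulation (4000 runs per setting) agrees: 25.0% when each group's fit is significant about 49% of the time, 16.0% at about 80%, 3.8% at about 96%. A two-sample test of the children's fits on the same data rejected in 4.7% to 5.3% of runs.

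These figures are for one model and one window. Over three windows, if independent, the chance of at least one TD-only pattern is 1 - (1 - 0.16)³ = 41% at p = 0.8 and 1 - (1 - 0.25)³ = 58% at p = 0.5. Windows from the same children are unlikely to be independent, so these are only a guide.

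**Step 2: TD-only pattern, unequal noise.** The probability becomes p(TD) × (1 - p(ASD)). With 0.8 and 0.5 it is 0.8 × 0.5 = 40%. Simulating identical encoding with ASD noise 25% higher (SD 1.0 vs 1.25) gave 38% to 45% across repeated simulations.

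**Step 3: direct group test, unequal noise, identical encoding.** Ranges are across repeated simulations.

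| Noise SD, TD vs ASD | Test on raw Spearman fits | Test on regression weights |
|---|---|---|
| 1.0 vs 1.25 | 9% to 11% | 3% to 7% |
| 0.5 vs 0.625 | 40% to 55% | 3% to 7% |
| 0.5 vs 0.75 | 83% to 94% | 3% to 7% |

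The Spearman test is worst where the signal is strong. There both groups fit the model almost always, so the TD-only pattern would seldom appear. The two problems therefore arise in different conditions, and guarding against one does not remove the other.

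**Step 4: why the weights hold.** The expected squared Euclidean distance between two stimuli is the true squared distance plus a term from noise. If noise is the same for all stimuli, that term is one constant, which the intercept absorbs. The standard has 980 trials against 980 / 7 = 140 per deviant, so pairs containing the standard carry less noise. This does not bias the weights: each feature differs in 4 of the 7 pairs with the standard and in 12 of the other 21, the same fraction (4/7).

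**Step 5: a correction that fails.** Dividing Spearman fits by split-half reliability still gave false rejection of 13% to 87% in the unequal-noise settings.

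**The case against.** A reader might infer that the trial's group conclusion rests on the TD-only pattern and so carries an error rate of up to a quarter. The documents do not support that. Step 3 names permutation testing of differences between groups, P5, P6 and P11 are group contrasts, and section 4 speaks of closer alignment, which is a comparison. The Discussion sentence sets no significance threshold, so reading it as significant versus not significant is one interpretation. Section 6 calls the findings preliminary. The 25% figure also needs about 50% power per group, which the protocol does not give; at 95% power the figure is 4.75%. All of this stands, and it confines the first part of the point to the wording in section 5.

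It does not remove that part. The sentence offers direct support from a pattern that cannot supply it, and exploratory status does not make the inference valid. Nor does the Step 3 test answer the noise problem if it is run on raw Spearman fits. That ASD data will be noisier is an assumption, as are the noise levels and the number of dimensions. The simulated encoding is additive, whereas P5 concerns a synergistic model.

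**Conclusion.** The point holds in a limited form. Section 5 permits a conclusion of different encoding from fit in TD and lack of fit in ASD, without requiring the between-group test in section 2.3.4. If it is applied as significant versus not significant, the false TD-only rate for one model and one window is p(1-p), at most 25% with equal power, and about 40% if ASD data are 25% noisier. The planned direct test keeps about 5% under equal noise. On raw Spearman fits with noisier ASD data it rejects from about 10% to about 90%, depending on signal and noise.

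The protocol's planned inference as a whole is not shown to have a 25% error rate, since a between-group test is written into the Methods. RSA power and the ASD noise excess are assumptions, so the sizes are ranges.

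**What to change.** In section 2.3.4 (Step 3) and section 5:

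- Compute model fit for each child. Base any statement that ASD encodes features differently only on the between-group permutation test of that measure (30 vs 30).
- State that fit in one group and not in the other is not evidence of a difference.
- As the primary or an accompanying between-group measure, use per-child weights from regressing squared Euclidean distances on the feature RDMs with an intercept, adding an interaction term for P5's synergistic model. Step 2 leaves the choice between Euclidean distance and Pearson correlation open, so Euclidean must be fixed for this analysis.
- Keep Spearman for comparing models within a group. Do not divide it by split-half reliability.

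The cost is wording in two sections and a small change of code, with no new data. The downsides are that some TD-only patterns can no longer be reported as group differences, and that the regression weights also reflect overall response amplitude, so a group difference in weights needs to be read with that in mind.
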